## Abstract

**Background:**

Vascular cognitive impairment, no dementia (VCIND) is a condition at risk for future dementia and should be the target of preventive strategies. Preliminary evidence suggests that acupuncture may be a clinically effective intervention for people with early-stage vascular cognitive impairment. We will do a multicenter, 6-month, drug-controlled, nonblinded, randomized, parallel-group trial to determine whether acupuncture is effective for improving cognitive function and quality of life for patients with VCIND.

**Methods/Design:**

A total of 216 eligible patients will be recruited and randomly assigned acupuncture for two sessions/week (n = 108) or citicoline 300 mg/day (n = 108) in a multicenter, 6-month trial. The primary endpoint is cognition (Alzheimer's Disease Assessment Scale, Cognitive Subscale (ADAS-cog)). Secondary endpoints include assessments of activities of daily living and behavioral symptoms (Clock Drawing Test (CDT), Activities of Daily Living (ADL) and Instrumental Activities of Daily Living scale (IADL)).

**Discussion:**

This will be the first large-scale trial specifically evaluating acupuncture therapy in VCIND. If the study confirms the effectiveness and safety of acupuncture treatment, it will be important to examine how the acupuncture approach could most effectively be integrated into the provision of routine healthcare.

**Trial registration:**

This study is registered as an International Standard Randomised Controlled Trial on 17 January 2014, number ISRCTN 82980206

**Electronic supplementary material:**

The online version of this article (doi:10.1186/1745-6215-15-442) contains supplementary material, which is available to authorized users.

## Background

Cerebrovascular disease is the second most common cause of cognitive disorders [1]. Vascular cognitive impairment (VCI) reflects cognitive disorders that are associated with vascular disease [2]. Some stroke-related factors such as multiple small or large strokes and ischaemic white-matter lesions have been associated with poststroke VCI. Six months after stroke, as many as 44 to 74% of patients present some degree of cognitive disturbance [3–5]. Stroke patients with cognitive impairment but no dementia have an increase in the 5-year risk of developing dementia of any type [6]. VCI with no dementia (VCIND) is a potentially treatable and preventable cause of dementia in later life, and familiarity with this condition will help the practitioner provide better care to patients [1]. Acupuncture is widely used for patients with cognitive disorders. It has been confirmed that acupuncture has positive effect on cognition and quality of life in patients who had a stroke [7]. However, there is no data on the effectiveness and safety of acupuncture used for VCIND patients. The aim of this study is to assess the effectiveness and safety of acupuncture in the treatment of VCIND patients.

## Methods/Design

### Design

The design is a three-center randomized trial (Figure 1). Two hundred and sixteen patients with VCIND will be recruited for inclusion in the study upon fulfillment of the selection criteria. The patients will be randomly allocated into the acupuncture treatment group (two sessions/week for 3 months) or the citicoline (Qilu Pharmaceutical Co., Ltd., Shandong, China) control group (100 mg/time, three times/day for 3 months). There will be a 3-month follow-up period. General ethical approval has been obtained from the ethics committee of the Beijing Hospital of Traditional Chinese Medicine affiliated to Capital Medical University on 22 March, 2013 (Ref: 201317) (Additional file 1).

**Figure 1 Fig1:**
[figure not shown]
**Flow chart.**

### Participants

Patients will be recruited in acupuncture clinics in the Beijing Hospital of Traditional Chinese Medicine Affiliated to Capital Medical University, the Beijing Chinese Medicine Hospital in Huairou District, the Beijing Fengtai Hospital of Integrative Medicine and the Dongzhimen Hospital Affiliated to Beijing University of Chinese Medicine.

### Inclusion criteria

Patients who meet all of the following conditions will be considered for enrollment. The inclusion criteria are as follows: subjects (males and females) age 55 to 85 years old; fluency in language sufficient to reliably complete all study assessments; a Hachinski score ≥7; evidence of vascular lesions based on neuroradiology; a Mini-Mental State Examination (MMSE) score > dementia threshold corrected according to the years of education (score >17, score >20 and score >24 for 0, ≤6, and >6 years of education, respectively); a Montreal Cognitive Assessment (MoCA) score <25 for ≤12 years of education or score <26 for >12 years of education; and signing of an informed consent form.

### Exclusion criteria

The exclusion criteria are as follows: history of mental diseases (for example, schizophrenia, serious anxiety and depression); Alzheimer's disease (AD), Parkinson's disease (PD), frontotemporal dementia (FTD) or Huntington's disease (HD); epilepsy and/or ever having antiepileptic drugs; or the presence of serious heart disease, kidney disease or liver disease.

### Interventions

After giving informed consent and completing a baseline evaluation, each participant will be randomized to the acupuncture treatment group or to the citicoline control group. The acupuncture treatment strategies are developed by consensus with experienced acupuncture practitioners and a neurologist. The acupuncture group will receive acupuncture at the Zusanli (ST36), Xuehai (SP10), Danzhong (RN17), Zhongwan (RN12), Qihai (RN6), Baihui (DU20), Fengfu (DU16), Xinshu (BL15), Yixi (BL45), Tongli (HT5) and Zhaohai (KI6) acupuncture points. Only sterile, stainless, single-use needles (Hwato, Suzhou, China) without guide tubes will be used. The gauge is 0.35 × 40 mm or 0.35 × 25 mm and the depth of insertion is 4 to 50 mm, depending on the location of the needle. Needles are correctly inserted and manually stimulated until the ‘De Qi’ sensation is elicited. ST36, SP10, RN17, RN12, RN6, and DU16 will be inserted 10 to 15 mm deep with a 0.35 mm × 40 mm acupuncture needle. DU20, BL15, BL45, HT5 and KI6will will be inserted 5 to 10 mm deep with a 0.35 mm × 25 mm acupuncture needle. The needles are retained for 20 minutes in every session. Other forms of acupuncture treatment (for example, laser acupuncture, electro-acupuncture or moxibustion) will not be permitted.

The citicoline control group will receive oral citicoline 100 mg/time, three times/day. A systematic review of the literature has revealed that citicoline is safe and effective in improving poststroke cognitive decline [8].

Treatment will be conducted over a period of 3 months, at a frequency of two sessions per week of acupuncture treatment group and three times per day for the citicoline control group.

### Education of acupuncturists

The participating acupuncturists will be members who have been qualified for at least 3 years, hold a Chinese medicine practitioner license from the Ministry of Health of the People’s Republic of China and take an educational course to ensure their strict adherence to the study protocol and familiarity with the administering study.

### Randomization

After signed informed consent and baseline measurements have been obtained, randomization will be performed according to a random list of numbers generated with SAS software (SAS Institute, Inc., Cary, NC, USA). The allocation list will be handled by an independent investigator who has no contact with the study participants and is not involved in the supervision of staff responsible for the collection of data. The allocation of the randomization sequence will be concealed centrally by telephone.

### Blinding

The interviewers who measured the outcomes will be blinded to the randomization status. It is not possible to blind participants due to the nature of the intervention. Blinding also will be maintained for data management, outcome assessment and data analysis.

### Primary outcome

A general cognitive performance battery will be evaluated using the Alzheimer's Disease Assessment Scale-Cognitive (ADAS-Cog). ADAS-cog is a quantitative instrument designed to assess the severity of cognitive impairment over time in Alzheimer’s disease patients, but it still is widely used for the cognitive assessment in mild to moderate vascular dementia [9]. The Chinese version of the ADAS-cog subscale has been determined to be reliable and valid among older Chinese in Hong Kong [10]. The adapted scale consists of 13 individual tests, including word recall, naming objects and fingers, commands, constructional and ideational praxis, orientation, word recognition, spoken language and comprehension, word finding and recall of test instructions. The ADAS-Cog requires approximately 30 to 45 minutes to administer, depending on the degree of cognitive impairment [11].

The ADAS-Cog will be assessed at baseline (before treatment initiation), the end of treatment and 3 months after the end of treatment.

### Secondary outcome measures

Cognition of the executive function and praxis will be evaluated using the Clock Drawing Test (CDT). Executive impairments have been found to be the most common functioning impairments following stroke [12]. The CDT assesses cognition, focusing on executive function and praxis in contrast to the more language-based Mini-Mental State Examination (MMSE) [13].

The longitudinal functional outcome will be evaluated using the Ability of Daily Living (ADL) and Instrumental Activities of Daily Living (IADL). The functional ability of patients with vascular cognitive impairment is gradually lost [14]. Measures of functional disability typically contain items that reflect limitations in performing the ADL or IADL. Combining IADL and ADL items together in the same scale would provide enhanced range and sensitivity of measurement [15].

The CDT, ADL and IADL will be assessed at baseline (before treatment initiation), the end of treatment and 3 months after the end of treatment.

### Other outcomes

The perceived credibility of treatment will be evaluated by the Treatment Credibility Scale (TCS) [16]. It is a five-item questionnaire ranging from 1 (not at all) to 5 (very confident). Items are averaged to provide a single treatment credibility score, with high scores reflecting high treatment credibility.

Adverse events (AEs) will be actively assessed by the trial physicians using a list at each session of acupuncture, including discomfort or bruising at the sites of needle insertion, nausea, or feeling faint after each acupuncture treatment. Adverse drug reactions like nausea and vomiting, dizziness, dry mouth, and itching will also be recorded.

The TCS and AEs will be assessed at the end of treatment.

Concomitant drugs will be recorded during the study, including those taken for the control of vascular risk factors (hypertension, diabetes, atherosclerosis, atrial fibrillation, APOE, homocysteine, etcetera), antithrombotic treatments for cardioembolism, and the use of antiplatelet agents for noncardioembolic stroke.

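### Adverse events have two stated timings, and active list-based elicitation is described only at acupuncture sessions, so any between-arm comparison is at risk of ascertainment bias

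*Protocol article*

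**What the plan says.** The Background section makes safety part of the purpose: "The aim of this study is to assess the effectiveness and safety of acupuncture in the treatment of VCIND patients".

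Other outcomes then makes three statements about AE collection:

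- For acupuncture: "Adverse events (AEs) will be actively assessed by the trial physicians using a list at each session of acupuncture". The examples given are needle-site discomfort or bruising, nausea and feeling faint.
- For drug reactions: "Adverse drug reactions like nausea and vomiting, dizziness, dry mouth, and itching will also be recorded". No assessor, method or contact is named.
- On timing, in the next paragraph: "The TCS and AEs will be assessed at the end of treatment".

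The Design section sets acupuncture at "two sessions/week for 3 months". Of the control arm, Interventions says: "The citicoline control group will receive oral citicoline 100 mg/time, three times/day". Neither section names a clinic contact for citicoline patients during treatment. Design adds: "There will be a 3-month follow-up period". The cognitive and functional outcomes are scheduled at baseline, at the end of treatment and 3 months later.

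**The concern.** The section gives two different times for one outcome, and the active method hangs on a contact that by definition occurs in one arm only. A site following the text could question acupuncture patients from a list twice a week and note citicoline reactions as they come to light.

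Four features of this trial make that matter:

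- The Abstract's Discussion anticipates a conclusion on the safety of acupuncture, and citicoline is the only comparator.
- The example symptoms overlap. Nausea appears for both treatments, and feeling faint is close to dizziness. A reader would compare exactly these.
- Participants are not blinded, so equal and structured enquiry is an important remaining safeguard for reported symptoms.
- Participants are enrolled for cognitive impairment (MoCA below the cut-off), so symptoms not asked about promptly may be forgotten.

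A difference in AE rates could then reflect how often patients were asked rather than what the treatments did.

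**Working it through.** The article states no AE rate, safety sample size or AE test, so there is no figure of its own to reproduce. The check has three steps.

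**1. Stated contacts.** Inputs: two sessions per week (Design), and 3 months taken as 12 to 13 weeks.

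- Acupuncture: 2 × 12 = 24 to 2 × 13 = 26 active enquiries, plus the end-of-treatment assessment.
- Citicoline: the end-of-treatment assessment is the only dated one. Other contacts are neither described nor excluded.

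**2. The AE timing sentence beside its neighbours.** The timing sentence for ADAS-Cog, and the one for CDT, ADL and IADL, each name baseline, end of treatment and 3 months after. The corresponding sentence for the TCS and AEs names the end of treatment alone. It does not mention the per-session enquiry set out just before it, so the two statements have to be reconciled.

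**3. What unequal capture could do (hypothetical).** None of the risks or capture fractions below comes from the article. Assume the same true AE risk p in both arms, full capture in the acupuncture arm, and a fraction r captured in the citicoline arm. The observed risks are then p and pr, and the apparent risk ratio is p/(pr) = 1/r.

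Take n = 94 per arm (the Sample size section's number before attrition), p₁ = p, p₂ = pr and p̄ = (p₁ + p₂)/2. The chance of a two-sided 5% result against acupuncture is

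Φ{ [ (p₁ − p₂) − 1.96·√(2p̄(1 − p̄)/n) ] / √([p₁(1 − p₁) + p₂(1 − p₂)]/n) }.

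| r | apparent risk ratio | p = 10% | p = 20% | p = 30% |
|---|---|---|---|---|
| 0.3 | 3.33 | 0.495 | 0.820 | 0.959 |
| 0.5 | 2.00 | 0.254 | 0.484 | 0.695 |
| 0.7 | 1.43 | 0.110 | 0.193 | 0.292 |
| 0.9 | 1.11 | 0.042 | 0.054 | 0.066 |
| 1.0 | 1.00 | 0.025 | 0.025 | 0.025 |

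With r = 1.0 the chance is the nominal 2.5% in that direction. With r from 0.9 down to 0.3 it runs from 4% to 96%.

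A second illustration, also assumed, uses a background symptom with 2% weekly risk in both arms over 13 weeks:

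- Full capture: 1 − 0.98^13 = 0.231.
- 50% of episodes recalled: 1 − 0.99^13 = 0.122, a gap of about 11 percentage points.
- 30% of episodes recalled: 1 − 0.994^13 = 0.075, a gap of about 16 percentage points.

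The width of these ranges shows that the mechanism can matter but that the document does not fix its size.

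**The case against.** A reader might infer more than the text supports, in four ways.

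- **That AEs are assessed only at the end of treatment.** The timing sentence contains no such restriction. Session-level enquiry plus an end-of-treatment assessment in both arms is a coherent reading. The wording is unclear rather than flatly contradictory.
- **That citicoline patients have no contact for 3 months.** This is inferred from silence. The article gives dosing and duration, not a visit schedule, and an article commonly leaves visit schedules and AE forms to the full protocol. For the same reason, the absence of a stated AE assessment at the follow-up visit is not an error in itself.
- **That each arm has its own checklist.** The symptoms are introduced as examples, and no second checklist is mentioned. Some difference is also unavoidable, because an oral drug causes no needle-site bruising.
- **That the safety comparison is biased.** No between-arm AE test is specified. Data analysis mentions a GEE for group differences in general terms, and the aim is worded as the safety of acupuncture, which close session-level recording serves well.

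The likely direction also tempers the point: over-counting under acupuncture works against the experimental treatment and would not manufacture a favourable safety result.

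All of this stands, and it limits the conclusion to a risk. It does not remove what the article does state: two timings for one outcome, and an active method tied to a contact that exists in one arm only.

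**Conclusion.** The point holds in limited form: as described, AE collection does not secure equal ascertainment, so a between-arm AE comparison carries a risk of bias. The only quantity that follows from the document is the 24 to 26 active enquiries per acupuncture patient. The expected direction, over-counting under acupuncture, assumes that citicoline patients are in practice asked less often or less actively, which the article neither states nor rules out. Every figure for the size of the effect is hypothetical. If the full protocol gives both arms the same method and contacts, what remains is a wording correction. If it does not, the plan should be changed while recruitment is under way, because events never asked about cannot be recovered at analysis.

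**What to change.** 1. Reconcile the two timing sentences: say what is collected at acupuncture sessions, what is collected at the end of treatment, and in which arm.
2. Base any between-arm AE comparison on one common checklist, made up of general symptoms plus both treatment-specific sets. Ask it in the same way in both arms at the two visits that already exist (end of treatment and 3 months after), and at any interim contact both arms share.
3. Report AEs elicited at acupuncture sessions separately and descriptively. They remain valuable for describing the safety of needling.

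The cost is one combined form and some wording. There are two downsides. Session-level events leave the comparative table. The common visits also rely on recall in cognitively impaired patients, and those prompted at each acupuncture session may remember more, so some asymmetry can persist. This should be stated as a limitation.

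### No adverse-event assessment is scheduled for the 3-month follow-up, although safety is a stated aim and the efficacy scales are measured again at month 6

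*Protocol article*

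**What the plan says.** The aim, at the end of Background, covers safety as well as effect: "The aim of this study is to assess the effectiveness and safety of acupuncture in the treatment of VCIND patients". The Abstract calls the study a "multicenter, 6-month, drug-controlled, nonblinded, randomized, parallel-group trial". Interventions sets the active period: "Treatment will be conducted over a period of 3 months". Design then adds: "There will be a 3-month follow-up period".

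For the primary scale, Primary outcome states: "The ADAS-Cog will be assessed at baseline (before treatment initiation), the end of treatment and 3 months after the end of treatment". Secondary outcome measures gives CDT, ADL and IADL the same three time points.

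Other outcomes has three sentences on harms:

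- A checklist during acupuncture: "Adverse events (AEs) will be actively assessed by the trial physicians using a list at each session of acupuncture".
- Drug reactions, with no visit or window: "Adverse drug reactions like nausea and vomiting, dizziness, dry mouth, and itching will also be recorded".
- The timing sentence, shared with the credibility scale: "The TCS and AEs will be assessed at the end of treatment".

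The same section says that concomitant medication is logged over the whole study, with no stop at the end of treatment.

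**The concern.** Each outcome in the article has its own schedule. The efficacy scales have a time point after treatment. AEs do not, although safety is part of the aim and the scales already require a month-6 visit. This is a written rule, not a detail lost when the full protocol was condensed: the article names the AE time point, and that time point is month 3.

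A site that follows the sentence has no scheduled prompt to ask at month 6 about a reaction that appeared late, one that had not resolved, or a serious event since treatment ended. Whether such an event reaches the database then depends on the patient volunteering it and the assessor noting it. A safety statement from a trial described as lasting 6 months would rest on systematic data from 3 months.

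The sentence also joins two measures with different needs. Treatment credibility can reasonably be measured once, at the end of treatment. AEs accrue over time, and one shared time point suits them less well.

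**Working it through.** **Inputs, all from the protocol article**

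- Treatment: 3 months (Design; Interventions).
- Follow-up after treatment: 3 months (Design).
- Trial length: 6 months (Abstract).
- Patients: 216, 108 per group; attrition allowance 15%; SD 5.89 (Sample size).
- AE time points: each acupuncture session, and the end of treatment (Other outcomes).

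**Step 1. Reproduce the stated trial length.** 3 + 3 = 6 months, which agrees with the Abstract.

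**Step 2. Set the schedules side by side.**

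| Measure | During treatment | Month 3 | Month 6 |
|---|---|---|---|
| ADAS-Cog, CDT, ADL, IADL | no | yes | yes |
| AE checklist (acupuncture arm) | each session | – | – |
| AE assessment | – | yes | not scheduled |
| Drug reactions | recorded, no window given | as left | as left |
| Concomitant drugs | yes | yes | yes (whole study) |

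The scales and concomitant drugs extend beyond month 3. No AE time point does.

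**Step 3. Share of observation time without a scheduled AE assessment.** 3 / 6 = 50%.

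**Step 4. In patient-years, before attrition.**

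- Total: 216 × 6/12 = 108.
- Follow-up: 216 × 3/12 = 54.
- With the 15% allowance taken off the whole follow-up period: 216 × 0.85 × 3/12 = 45.9.

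**Step 5. After the fix.** AE assessment would span 6 of 6 months, or 108 planned patient-years instead of 54.

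**Step 6. Could missed events distort the month-6 ADAS-Cog comparison?** The documents give no event rate and no effect of an event on the scale, so this is an illustration only. Assume 2 recurrent vascular events in one arm, none in the other, and a 10-point worsening for each.

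- Patients per arm after attrition: 108 × 0.85 = 91.8, about 92.
- Shift in that arm's mean: 2 × 10 / 92 = 0.22 points.
- Standard error of the difference: 5.89 × √(2/92) = 0.87 points.
- Ratio: 0.22 / 0.87 = 0.25.

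Even with a deliberately lopsided split, the shift is about a quarter of one standard error. Randomisation gives no reason to expect the split to fall that way.

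**The case against.** The best defence is that an AE window matched to exposure is a legitimate choice. Neither study treatment is given in months 3 to 6. The reactions listed in Other outcomes (needle-site discomfort or bruising, nausea, vomiting, faintness, dizziness, dry mouth, itching) are mostly immediate. The aim speaks of safety in treatment and promises no off-treatment data, and the 6-month label describes trial length, not the AE window. Nothing forbids noting an event mentioned at month 6. Serious-event reporting and visit forms may well be in the full protocol, which is not shown. Recording concomitant drugs throughout could leave a trace of a new vascular event.

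Most of this stands, and it limits the size of the point. It does not remove it: the AE time point is stated and stops at month 3, and a medication log is no substitute for asking about events.

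A reader might infer more than the text supports:

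- **That half the trial is unmonitored.** The text shows only that no AE assessment is scheduled there.
- **That a known number of strokes would go unrecorded.** The article gives no event rate. It says antithrombotic and antiplatelet drugs will be recorded, not how many patients take them.
- **That month-6 effects could not be told apart from new strokes.** The illustration in the working does not bear this out.
- **That every patient will be seen at month 6.** Sample size allows for 15% attrition.

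**Conclusion.** The point holds in a limited form. The written AE schedule covers 3 of the 6 months and leaves 54 of 108 planned patient-years (45.9 if the 15% attrition allowance is taken off all of follow-up) without a scheduled assessment, in a trial that states safety as an aim and already plans a visit at month 6. Delayed, persisting or serious events in follow-up may be missed or captured unevenly.

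The consequence is modest, since neither study treatment is given then and most listed reactions are immediate. This is a cheap improvement to data collection. It is neither an internal contradiction nor a threat to the primary comparison.

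The 50% figure rests only on the stated schedule and needs no outside assumption. The conclusion assumes that the sentence under Other outcomes is applied as written. If the full protocol already schedules AE enquiry at month 6, only the wording of the article needs correcting.

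**What to change.** Split the shared sentence under Other outcomes. Let the TCS keep its single assessment when treatment ends. State separately that AEs are assessed in both arms at two points: the end of treatment, and the visit 3 months later at which the scales are already measured. Keep the checklist at acupuncture sessions as it is.

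At month 6, ask each patient about any event since the last visit and record its date. Report AEs separately for the treatment period and the follow-up period, so that on-treatment reactions are not mixed with later events.

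If month-6 ADAS-Cog results are also described by whether a patient had a recurrent vascular event, keep that description outside formal testing. Such an event happens after randomisation and treatment might influence it, so the comparison of all randomised patients should stay unchanged.

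The cost is one line in the visit schedule, one form and a few minutes per patient at an existing visit. Some late events unrelated to treatment will also be recorded. Trial status says recruitment is under way, so the change can still help patients who have not yet reached month 6.
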